#### Follow-up phase

The follow-up questionnaires will be sent to the former participants six and twelve months after the rehabilitation treatment by the university. Postal reminders will be send after three weeks if the questionnaire has not been sent back by patients.

#### Drop out criteria

Dropouts are defined as patients who do refuse to participate in the study at the end of the rehabilitation program. These patients will not be contacted after six and twelve months for further evaluation.

Also, dropouts are patients who withdraw the entire study participation and prohibit the use of existing personnel data. In this case, the questionnaire filled out at the beginning of the rehabilitation program must be given to the patient.

If patients don’t fill out the questionnaire at the end of the rehabilitation (despite former reminder), they will still receive a questionnaire after six and twelve months, if they don’t explicitly refuse or withdrew from the study participation.

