**Motivational and volitional determinants of physical activity**						
	risk perception (3 items), self-efficacy (3 items), outcome expectancies (11items), experiences with physical activity (5 items), self-concordance (12 items), intention (7 items), action (4 items) and coping (4 items) planning, action control (6 items)	x	x	x	x	[63-67]
Stage of change algorithm for physical activity	two Items (Have you performed moderate physical for 30 minutes or longer on a minimum of 3 days per week? and "Since when are you as regularly active as you are now?"; possible answers: 1. Question: no, and I don’t intend to do so; no, but I am thinking about doing so; no, but I have the strong intention to do so; yes, but it is difficult to me; yes, and it is easy for me; 2. Question: open)	x	x	x	x	[68,69]
**Attitudes towards performing physical activity**	modified Version of Short-Questionnaire to measure cognitive and affective attitudes toward sports activities	x	x	x	x	[70]
**Treatment satisfactions with exercise therapy**	18 items (e.g. “I would recommend the exercise therapy other patients.” measured by using a six-point ordinal scale with 1= “absolutely agree”, 6=“absolutely disagree”; e.g. “The time extent of the exercise therapy, I perceived as…” measured by using a five-point ordinal scale with 1=“far too high“, 5=“far too low“; e.g. “Overall, how do you rate the exercise therapy?” measured by using a six-point ordinal scale with 1= “very satisfied”, 6=not “satisfied at all”)		x			self-designed
**Treatment satisfactions with the rehabilitation process**	five items (e.g. “Overall, how do you rate the rehabilitation process?”) measured by using a ten-point ordinal scale (1= “very poor”, 10 = „excellent“)		x			self-designed

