#### Primary outcome measure

We will use the level of functional limitations associated to clbp twelve months after the end of BMR measured by the Hannover Functional Ability Questionnaire (FFbH-R) as our primary outcome [51]. The FFbH-R consists of twelve items with a three-stage answering scale. Its summary score describes the low back pain associated functional ability in activities of daily living in adults on a scale of 0% (minimum functional ability) to 100% (maximum functional ability). The questionnaire is constructed for response to already light and moderate functional restrictions. The average item intercorrelation amounts to 0.50. The test-retest-reliability with repeated measures after approximately one week is above 0.75, Cronbach alpha figures 0.90 [51]. The one factorial structure of the instrument was confirmed in a principal component analysis. The FFbH-R is comparable to the internationally used Roland Morris Questionnaire for measuring clbp related disability with a correlation of 0.75 [73].

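### Patients who refuse at discharge lose all 6- and 12-month contact without being asked whether they would still give the 12-item primary outcome

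*Protocol article*

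**What the plan says.** The Drop out criteria section of the protocol article distinguishes three situations.

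- **Refusal at discharge.** "Dropouts are defined as patients who do refuse to participate in the study at the end of the rehabilitation program". The consequence follows directly: "These patients will not be contacted after six and twelve months for further evaluation".
- **Full withdrawal with a ban on data use.** "Also, dropouts are patients who withdraw the entire study participation and prohibit the use of existing personnel data". The baseline questionnaire is then handed back to the patient.
- **Discharge questionnaire not filled in, without refusal.** For these patients, "they will still receive a questionnaire after six and twelve months, if they don’t explicitly refuse or withdrew from the study participation".

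The Primary outcome measure section sets the endpoint: "We will use the level of functional limitations associated to clbp twelve months after the end of BMR". It also gives the length of the instrument: "The FFbH-R consists of twelve items with a three-stage answering scale".

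For forms not returned at six and twelve months, the Follow-up phase section says: "Postal reminders will be send after three weeks if the questionnaire has not been sent back by patients". Data analysis provides for intention-to-treat with multiple imputation for dropouts and withdrawals. Sample size and power calculation budgets for 40% dropout.

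**The concern.** The first group is told apart from patients who forbid use of their data, yet its primary endpoint is given up at t2, about twelve months before t4. No intermediate answer is described, such as declining further full questionnaires but accepting the short primary form. The full set is long, and some refusals may concern that burden more than the study itself, although the document does not say why patients refuse.

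Two things are at stake. The first is selective loss. Refusal at this moment comes straight after the assigned exercise programme, so its frequency or its reasons could differ between arms. The second is weak information for imputation. A refuser who also leaves the t2 form blank contributes only t1 data, and Table 3 collects satisfaction with treatment, a plausible driver of refusal, at t2 alone. The planned non-responder analysis does not help here, because it covers eligible patients who never join.

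**Working it through.** **1. The plan's own figures.** Inputs from Sample size and power calculation: d = 0.5 (f = 0.25), alpha 5%, power 80%, ANCOVA at t4, 40% dropout. Sidedness is not stated.

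- A two-sided, two-sample t-test needs 63.8 per arm, so 64 per arm and 128 in total. A two-sided ANCOVA F-test with one covariate gives power 0.801 at N = 128. A one-sided calculation (normal approximation) would give 100 and does not match.
- 128 / (1 − 0.40) = 213.3, rounded up to 214.

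Both stated numbers reproduce.

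**2. Questionnaire burden at t2 (Table 3).**

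- Motivational and volitional block, which begins "risk perception (3 items), self-efficacy (3 items), outcome expectancies (11items": 3 + 3 + 11 + 5 + 12 + 7 + 4 + 4 + 6 = 55 items.
- Satisfaction: 18 + 5 = 23 items.
- Eleven other instruments or item sets: NRS, GCPS, PHQ-D, GAD-7, SF-12, PSS, FESV, AEQ, TSK, stage of change, attitudes.
- FFbH-R: 12 items.

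The primary endpoint needs only the last line.

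**3. Patients affected by the rule.** The document gives no refusal rate at discharge. Assumed rates applied to 214:

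- 2%: 0.02 × 214 = 4.3
- 5%: 0.05 × 214 = 10.7
- 10%: 0.10 × 214 = 21.4

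**4. Precision if some of them accept the short form.** The starting point is 0.60 × 214 = 128.4 evaluable, power 0.803. Refusers are taken to be part of the budgeted 40%.

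| Assumption | Evaluable | SE ratio, sqrt(128.4 / N) | Power at d = 0.5 |
|---|---|---|---|
| 2% refuse, all accept | 128.4 + 4.3 = 132.7 | 0.984 | not computed |
| 10% refuse, half accept | 128.4 + 10.7 = 139.1 | 0.961 | 0.833 |
| 10% refuse, all accept | 128.4 + 21.4 = 149.8 | 0.926 | 0.860 |

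The last row is an upper limit under these assumptions.

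**5. Possible bias.** Suppose missing patients are D standard deviations worse than observed ones in both arms, and imputation does not explain that gap. The observed mean in an arm with missing share p is then too high by p × D, and the treatment contrast is biased by (difference in p) × D.

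- A 10-point difference between arms (for example 35% against 45% missing) with D = 0.2 to 0.5 gives 0.02 to 0.05 SD.
- A 20-point difference (30% against 50%) gives 0.04 to 0.10 SD.
- Equal missing shares and equal D give zero.

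The planned effect is 0.5 SD. For discharge refusals alone to create a 20-point difference at a 10% overall rate, every refusal would have to fall in one arm (0% against 20%). The lower range is therefore the more relevant one here, and even that is illustrative.

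**The case against.** The strongest reply is that these patients refuse the study and not merely a long form, and that Ethical aspects lets participants stop at any time without disadvantage. Leaving them alone respects that. This stands, and recovery cannot be assumed: the short form helps only if it is offered when the patient refuses and is freely accepted. It does not follow that the question should go unasked, provided that a full refusal ends all contact.

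A reader might infer several stronger points that the document does not support:

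- *The follow-up rules are all or nothing.* They are not. Patients who only miss the t2 form are still mailed at six and twelve months.
- *Non-returners are reminded only about the full set.* The Follow-up phase section does not say what the reminder contains. A condensed article may leave a short form or another contact route to the full protocol.
- *Patients react to an unblinded programme.* Therapists are unblinded, but the Blinding section masks patients to the study group and tells them that both programmes meet current standards. They still experience different programmes, so arm-related refusal is possible, but no figure shows it.
- *The trial is underpowered because of this loss.* The 40% is already budgeted.

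The argument about missing satisfaction data applies to refusers who skip t2. Patients who complete t2 and are lost later do have t2 FFbH-R and satisfaction data that imputation can use.

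**Conclusion.** The point holds as a minor weakness of a rule that the article states explicitly. A refusal at discharge ends collection of the 12-month FFbH-R without the patient being asked about the primary form alone. It is not a contradiction and not a sample-size error.

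The size is unknown. About 4 to 21 patients would be affected if 2% to 10% refused. The gain in power would be at most from 0.80 to 0.86, and that needs both the highest assumed refusal rate and full acceptance. Bias arises only if refusal differs by arm, or if the unexplained gap between missing and observed patients does. At a 10-point arm difference it would be 0.02 to 0.05 SD. The case for a change rests on its low cost and on imputation being weakest where only baseline data exist.

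**What to change.** In Drop out criteria, record at discharge which of two things a refusing patient declines:

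- (a) further full questionnaires, while agreeing to receive the FFbH-R alone at six and twelve months; or
- (b) any further contact.

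Stop mailing only for (b). Leave the existing rules for full withdrawal and for a missed t2 form as they are. Mention the reduced option in the consent form, and report the number in (a) and (b) by arm.

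Optionally, and only if the full protocol does not already do so, enclose an FFbH-R-only sheet with the existing three-week reminder.

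The cost is a tick-box, a consent sentence and possibly one extra sheet in a letter already sent. The downside is that a few patients may choose the short form over the full set, giving slightly fewer data for the secondary hypotheses.

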#### Registration of non-responders

The registration of all eligible patients and the reporting of the number and the sex of eligible patients who do not participate (non-responder analysis) during the time of the study will take place for the identification of selection effects during the recruitment process.

### Randomisation

The randomisation procedure of the participants takes place with an online-based randomisation feature. Therefore, we implement a central data base for electronic data recording which will be used in each of the two rehabilitation centres. An independent administration employee, who is not involved in the study, will use the online-based randomization feature within each rehabilitation centre to register eligible participants via a web application. After registration, the online-based randomisation feature automatically accomplishes the allocation to one of the treatment groups.This system has been developed in a prior study [38] and incorporates the existing national data protection regulations. Clear advantages of this procedure are a prompt randomisation and a concealment of the sequence of allocation. For sequence generation we use an “urn randomisation”-algorithm [39]. It has good statistical properties [40] and can be used to stratify by different criteria. In this study we stratify for “rehabilitation centre” with the two rehabilitation centres and “gender” with two categories. Additionally, a structural equality by chance concerning both sub-samples is ensured.

The randomisation process of patients will be planned together with the staff of the participating rehabilitation centres, especially the medical directors, administration staff, system administrator and those responsible for therapy planning in the rehabilitation centres during the phase of preparation and implementation. For the planning of the randomisation process, the implementation of the data base and the training of administration staff to handle the data base, the rehabilitation centres will be visit two to three times.

### Sample size and power calculation

Thinking of the short-term effectiveness of both interventions, only small differences between groups and small effect sizes at the end of rehabilitation (t2) (d=0,3 or f(V)=0,15) are expected to be found [12,41,42]. Because of the minor long-term effects of the present usual care, medium effect sizes (d=0,5 or f(V)=0,25) are expected to be found at six and twelve months. This is in line with Friedrich and colleagues [43,44], who were able to show medium effect sizes regarding a reduction of disability when comparing a functional exercise therapy to an exercise therapy which contained additional motivational strategies (Disability Score: d~0,68). Sample power (Software: G-Power 3.0) concerning the primary outcome was approximated for an analysis of covariance at t4 with medium effect size of Cohen’s d=0,5, alpha error 5% and test power of 80%. This approximisation results in a sample size of at least 128 patients without missing values. Anticipating a dropout rate of 40%, it is necessary to include 214 patients (n=107 for each group).

### Interventions

#### Control arm

Both of the participating rehabilitation centres have a conceptually similar BMR for patients with orthopedic functional impairment and concurrent substantial psychological or social component of this impairment. The behavioural medical concept takes into account the biopsychosocial mechanisms relevant for the chronification of musculoskeletal disorders [9,45]. Empowerment and self-management are encouraged. On average, the BMR lasts for 27 days. Compared to the traditional multidisciplinary inpatient rehabilitation, the BMR has specifically defined inclusion criteria [11]: 1) an interdisciplinary admission, 2) a standardized psychosocial assessment, 3) a reconciled interdisciplinary case management, 4) case reviews on a regular basis, 5) supervision, 6) closed groups (a group remains together in all treatments during their whole stay at the rehabilitation centre), 7) the possibility of an individually tailored rehabilitation schedule and 8) therapist consistency for the most part (a therapist accompanies a group throughout a whole intervention). The multiprofessional core of the BMR relies on psychological interventions and standard exercise therapy (SET), in which ten to twelve patients take part together as a closed group. Other interventions are presentations with information about health and health behavior, rehabilitation/social counseling and if necessary occupational therapy. The total extent of therapy during the stay in the rehab centre is 65 hours on average, including approximately 26 hours exercise therapy. An experienced orthopedist bears the overall responsibility. A detailed description of the psychological group and exercise therapy group is available in the Additional files (see Additional file 1).

#### Intervention arm

Participants in the intervention arm will also receive a BMR, but with a specific behaviour-oriented exercise therapy (BET), which replaces SET. BET has been developed on the basis of previous work [46]. In general, BET aims at facilitating health-related knowledge and skills, which empower patients to maintain a healthy, physically active lifestyle beyond their BMR treatment. It’s based on the assumption that a theory-based, systematic and integrated targeting of relevant psychosocial factors in the chronification of low back pain and also determinants of health behavior change, as well as factors of physical deconditioning and disuse improves the self-management and therefore reduces functional impairment of patients with clbp. This is reached by a structured combination of exercise, education and behavioural elements with a strong emphasis on patients’ preferences and their previous experiences with exercise. Therefore different types of exercise are considered for patients to become familiar with their execution (e. g. methods of controlling intensities and training progression), as well as to encourage positive experiences with exercise. BET is delivered in closed groups with six to twelve patients during the approximately four weeks of the BMR. In total, exercise therapy comprised an extent of 26 hours on average. Both the fifteen sessions and the related modules of BET are guided by the same trained BET-therapist.

#### 15 BET sessions, 60 minutes duration

The major part of BET consists of fifteen sessions with duration of 60 minutes each. Every single session comprises an introduction (approx. 5min), structured active play (approx. 5min), short education periods on selected topics (approx. 10min), exercises and relaxation (approx. 30min) as well as conclusion and sporadically a metaphoric story (approx. 10min). The entire thematic topic overview of the fifteen sessions can be seen in the in the Additional files (see Additional file 2).

#### BET related modules, 20 to 60 minutes duration

In the first week patients receive, two 60 min. introductions in weight-lifting training, two 60 min. introductions in an aerobic exercise (walking, nordic walking and ergometer cycling) and two 30 min. introductions in aqua training (aqua aerobics, aqua jogging). Further three modules of planning out of every 60 minutes duration are distributed over three weeks. The purpose of these related modules is for patients to become familiar with different types of exercises in the first week supervised by a BET-therapist followed by a more self-directed planning and performing of exercises during the rehabilitation stay. Therefore during the four weeks of treatment the supervision by the therapist decreases, while the performing of self-directed exercises increases. At the end of the second week, the BET-therapist will reflect together with the group reviewing, how well the individual realisation of planned exercises itself is managed. If barriers occur, they will be discussed and alternative possibilities will be developed. To be available for consult in case of any questions especially related to weight-lifting training, additional three appointments will be scheduled (one each in the 2nd to 4th week of therapy) under supervision of a BET therapist. Table 2 shows the volume of related modules with duration, frequency and distribution over the four weeks of the rehabilitation phase.

**Table 2 T2:** BET related modules

**BET related modules**	**Duration**	**Frequency/ week of rehabilitation**
Weight-lifting training introduction	60min	2x/ week 1
Weight-lifting training	60min	3x distributes over week 2 to 4
Aerobic exercise introduction	60min	2x/ week 1
Aquatic training introduction	30min	2x/ week 1
Planning module	60min	3x distributes over week 1 and 2
Individual physical activity/ exercise	----	self-directed physical activity/ exercise distributes over week 2 to 4

In summary, the following key features characterized BET:

– Patient-centred approach through active participation of patients in the entire treatment process and considering their individual preferences and previous experiences with exercise

– Goal-oriented combination of exercise, education, and behavioural elements within the BET

– Psychosocial factors that contribute to the chronification of clbp (e. g. pain-related cognitions, avoidance behavior, endurance behaviour) are systematically modified by the use of structured contents and methods which refer to exercise, education and behavioural elements

– Theory-based use of behavioural techniques to influence motivational and volitional determinants of health behavior change to promote long-term maintenance of self-directed physical activity

– Specific patient-oriented, plain media and materials with a very demanding character are used

– Trainer manual with a detailed description of the BET program for a standardized execution of the exercise, educational and behavioural elements, as well as a standardized use of media and materials to achieve multidimensional objectives of the BET is available

– Objectives, contents and methods of BET are matched in terms of a consistent approach and cooperation of all professions involved in the BMR

– Key messages and competencies trained by medical and psychological professions in the BMR will be reflected and reinforced within the BET.

More information can be found in the Additional files (see Additional file 3) and the detailed trainer manual is available in German and can be requested from the authors.

#### Treatment adherence

The therapists who perform BET in the intervention group will receive an intensive training on the objectives, contents, structure, components and methods of the program. During the implementation phase two workshops (each 2 days with 720 min duration) at intervals of eight weeks will take place together with all BET-therapists from both rehabilitation centres. The workshops are provided on the basis of a manualised intervention concept and are delivered by the same trainers. Moreover, pilot groups with the BET program will be performed within the implementation phase. The BET-therapists are skilled in the use of the program and try out the approach with the specific goal-orientated components as well as the media and materials.

The intensive training of BET-therapists and the implementation of the BET-groups will be supervised and evaluated. For data collection, quantitative methods are used (self-constructed questionnaires). The acceptance of the therapists (motivation, readiness to change, and program satisfaction) and difficulties during the implementation as well as acceptance of the patients (program satisfaction) will be recorded.

Both exercise programs (SET and BET) within the BMR have the same duration. The duration of both exercise programs as well as additional interventions within the BMR are documented for each study patient during the intervention phase.

A potential source of bias in the execution of RCT in the inpatient rehabilitation is the potential mixture between the study group and the control group through a communication about intervention contents between patients as well as therapists within each rehabilitation centre. The adaptations in the BET aimed at the integration of behavioural techniques and a modified use of teaching approaches. A reflected effective exchange of the adapted intervention contents requires extensive knowledge of the underlying theoretical models of the chronification of lbp. This is generally not expected from patients of a BMR. In addition, the patients of both study groups will be informed that both exercise programs within in the BMR are of high quality and will be delivered based on actual scientific evidence.

Trained BET-therapists will sign a written contract concerning discretion about objectives, contents, structure, methods, media and materials used within the BET. Regularly, announced visitations during the intervention phase will occur in order to assure adherence to the treatment protocol. Individual deviations from the treatment protocol will be recorded. In the case of vacation or sick leave, a trained BET-therapist for replacement is available.

